#### Co-variates

Co-variates collected at cohort entry and annually thereafter are: age, sex, year of cohort entry, HbA1c (continuous), diabetes duration (time between diabetes diagnosis and cohort entry, continuous), BMI (continuous), serum creatinine (continuous), metformin use (yes, no), insulin use (yes/no), history of cancer (no non-melanoma skin cancer) (yes, no) and smoking (ever, never, unknown).

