## Background

Patients diagnosed with type 2 diabetes (T2D) are at increased risk for developing cancer; especially the risk of obesity-related cancers [1–5]. According to the most recent World Cancer Research Fund (WRCF) definitions obesity related cancers include oesophageal cancer, liver cancer, kidney cancer, stomach cardia cancer, colorectal cancer, advanced prostate cancer, post-menopausal breast cancer, gallbladder cancer, pancreatic cancer, ovarian cancer and endometrial cancer [6].

In addition to T2D and obesity, glucose-lowering agents used in the treatment of T2D have also been associated with cancer risk and some studies have reported that these relations can be drug specific. For example, the use of pioglitazone, not rosiglitazone, has been linked to the development of bladder cancer in some studies [7, 8], although the robustness of the evidence underlying this possible relationship remains unclear and was absent in recent reports [9, 10]. Also, insulin glargine has been linked to higher breast cancer risk in some studies [11], although - again - several studies reported no or even an inverse association [11–13]. Metformin has more consistently been associated with a decreased cancer risk [14], however concerns have been raised that this association might have been influenced by several types of bias [15, 16].

The sulfonylureas (SUs) are one out of six classes of oral glucose-lowering agents advised by the EASD and ADA as a second step when the glycaemic treatment targets are not reached with metformin mono-therapy [17]. Sulfonylureas have been available for many years and are highly efficacious at low costs. In the Dutch primary care treatment guideline for T2D, gliclazide is the preferred SU, as opposed to both the ADA and EASD which do not recommend a specific SU [17]. Previous studies have shown that within the class of SUs differences exist with regard to hypoglycaemia risk [18], for example there have been no reports of severe hypoglycaemia events in gliclazide users [18]. In addition, within-class differences in risk of cardiovascular events and safety when prescribed to patients with renal failure have been reported [19, 20].

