#### ZODIAC

The ZODIAC cohort is part of an ongoing primary care prospective study initiated in 1998, in which annually collected data are used for care improvement, benchmarking and research [25]. Patients consented with the anonymous use of their data for study purposes. Patients included are diagnosed with T2D and are exclusively treated in primary care in a shared care setting. Data on age, sex, date of T2D diagnosis, HbA1c, length, weight, estimated GFR, creatinine, albumin-creatinine ratio (ACR), cholesterol/HDL ratio, blood pressure, macrovascular complications (myocardial infarction, TIA, CVA) medication use (both diabetes-specific and other medication), smoking (yes/no) and alcohol use (yes/no) are recorded.

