#### Primary analysis

Descriptive statistics will be used to characterize the patients at cohort entry.

Time dependent cox proportional hazard analyses will be used to estimate the adjusted hazard ratio of developing obesity-related cancer when using gliclazide compared to other SUs (both individual and grouped as non-gliclazide SU). Exposure to SUs will be included as the cumulative number of years exposed to a specific SUs. Exposure status for SU will be updated annually. The primary analyses will be corrected for the previously mentioned confounders measured at baseline.

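### Recorded macrovascular history is left out of the adjustment set without a reason, so some residual confounding of the within-class SU hazard ratio may remain

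*Protocol article*

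**What the plan says.** The ZODIAC section of the protocol article lists what the cohort records. This includes "macrovascular complications (myocardial infarction, TIA, CVA) medication use (both diabetes-specific and other medication), smoking (yes/no) and alcohol use (yes/no) are recorded".

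The Co-variates section then names the adjustment variables one by one. It opens with "Co-variates collected at cohort entry and annually thereafter are: age, sex, year of cohort entry, HbA1c (continuous), diabetes duration" and continues with "BMI (continuous), serum creatinine (continuous), metformin use (yes, no), insulin use (yes/no), history of cancer (no non-melanoma skin cancer", followed by smoking in three categories (ever, never, unknown). Nothing in the wording marks these as examples. Macrovascular complications are not among them.

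The Primary analysis section ties the model to that list: "The primary analyses will be corrected for the previously mentioned confounders measured at baseline". The Secondary analyses section lets confounders vary over time and names metformin and insulin use, but adds no vascular history. Neither the two subgroup analyses nor the six sensitivity analyses add it.

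In the Background, the article states that "within-class differences in risk of cardiovascular events and safety when prescribed to patients with renal failure have been reported".

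**The concern.** This is a non-randomised comparison of drugs within one class, so the hazard ratio depends on the adjustment set covering recorded characteristics that could plausibly influence both the choice of SU and cancer risk. Macrovascular history is a candidate on both counts.

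- **Choice of SU.** The article itself reports that SUs differ in cardiovascular event risk. A prescriber aware of this might treat a patient with a previous infarction or stroke differently from one without.
- **Cancer risk.** Smoking is recorded only as yes/no and modelled in three coarse categories. Amount and duration are not captured. Vascular disease could be a marker of that uncaptured exposure. Lung and bladder cancer are named endpoints, and kidney and pancreatic cancer belong to the primary composite (Table 1).

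If both links exist, part of the gliclazide-versus-other-SU hazard ratio would reflect who received which drug. The Discussion says that even a minimal change in cancer risk could matter at population level and that the result could inform the choice of a specific SU. A distortion of a few percent is relevant to that use.

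**Working it through.** **Step 1: compare the lists.**

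| Item | Recorded (ZODIAC) | In Co-variates | Added in secondary, subgroup or sensitivity analyses |
|---|---|---|---|
| Macrovascular complications (MI, TIA, CVA) | yes | no | no |
| Smoking | yes/no | ever/never/unknown | no refinement |
| Creatinine | yes | yes | updated mean in secondary models |
| Estimated GFR | yes | no | no |
| Age, sex | yes | yes | endpoints evaluated separately by sex |

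The omission of macrovascular history is complete and unexplained.

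**Step 2: size of the possible distortion.** The article gives no vascular prevalence by SU and no risk ratio, so there is no figure of its own to reproduce. Every input here is an assumption. For an omitted binary confounder, the factor by which the hazard ratio is multiplied is approximately

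B = [1 + (RR − 1)·p1] / [1 + (RR − 1)·p0],

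where p1 and p0 are the prevalences of vascular history in the two SU groups, and RR is its residual association with cancer after the listed covariates.

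| Residual RR | p1 = 20%, p0 = 25% | p1 = 20%, p0 = 30% |
|---|---|---|
| 1.0 | 1.000 | 1.000 |
| 1.2 | 1.04/1.05 = 0.990 | 1.04/1.06 = 0.981 |
| 1.5 | 1.10/1.125 = 0.978 | 1.10/1.15 = 0.957 |

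The distortion runs from 0 to 4.3% downward. If the groups are swapped it runs upward: 1.15/1.10 = 1.045 in the last cell. Nothing in the article says which SU would have more patients with vascular disease, so the sign is open.

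**Step 3: what a larger figure would need.** An 8% distortion needs a residual RR of 2.0 and a 10-point gap: 1.20/1.30 = 0.923. About 9% needs RR 1.5 and a 20-point gap (35% versus 15%): 1.175/1.075 = 1.093. The documents support neither set of inputs.

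**Step 4: is renal function also missing?** ZODIAC records "estimated GFR, creatinine, albumin-creatinine ratio (ACR", and only creatinine enters the model. Taking eGFR to be creatinine-based (an assumption; the article does not name the equation), it is calculated from creatinine, age and sex. All three are covariates. A simulation used assumed inputs: mean age 67 (SD 11), half women, SD of log creatinine 0.20 to 0.35. Linear creatinine, age and sex explained 91-96% of the variance of a CKD-EPI-type eGFR and 74-90% of an MDRD-type eGFR, with nearly the same values within each sex. The remainder is functional form, not an unmeasured variable.

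**The case against.** **The Background does not describe prescribing.** The cardiovascular sentence concerns outcomes on the drugs. It does not say that patients with prior vascular disease are given a particular SU. The one influence on choice that the article states is the Dutch primary care guideline's preference for gliclazide, which is not linked to vascular history. A reader might infer that channelling by vascular disease is established and is carried into the hazard ratio. The documents do not support that; they make it plausible, no more.

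**The link to cancer is assumed.** Nothing in the article says that vascular history predicts cancer once age, sex, BMI, smoking, HbA1c, diabetes duration and creatinine are in the model. With no residual link the bias is exactly zero. This stands, and it is why the range in the working starts at RR 1.0. Vascular history is also only an indirect proxy for smoking intensity, and nothing shows how much of that confounding it would remove.

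**Renal function.** A reader might infer that using creatinine instead of eGFR leaves renal channelling uncontrolled. It does not: age and sex are in the model and endpoints are evaluated by sex. Preferring eGFR is a choice of functional form.

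**Timing.** Baseline is ZODIAC entry, and some patients may already be on an SU then. A vascular event recorded at entry could postdate SU start and even be a consequence of it. That is a fair limit, but it applies equally to baseline BMI and HbA1c, which are adjusted for. It shapes the wording of the fix without defeating it.

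**Left to a fuller plan?** An article may leave details to another document. Here it names the adjustment variables individually and binds the primary model to them, so the point concerns what it fixes. Nor does the article state a target effect size, so it cannot be said that the study was designed to detect small differences.

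**Conclusion.** The point holds in limited form. A recorded and plausible confounder is missing from the stated adjustment set, no reason is given, and no planned analysis tests the effect of leaving it out. Some residual confounding of the gliclazide-versus-other-SU hazard ratio may remain. Its direction is unknown. Its size is 0 to about 4%, assuming vascular prevalence of 20% versus 25-30% between SU groups and a residual cancer risk ratio of 1.0 to 1.5; at a risk ratio of 1.2 it is 1-2%. These are illustrative inputs, not estimates from the documents. The omission is not evidence that the hazard ratio will be biased, and it does not extend to renal function.

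**What to change.** Add macrovascular history (any of MI, TIA or CVA, yes/no) to the Co-variates list, so that it enters both the primary and the secondary models. Measure it at the same baseline as the other covariates. Keep that baseline value in the secondary models as well, since a vascular event during follow-up could itself result from SU exposure.

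The second planned sensitivity analysis already re-measures confounders in the year preceding the first SU prescription. Use the vascular value from that year there. This addresses the timing limit wherever such a record exists.

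Keep serum creatinine; no change to eGFR is needed.

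The cost is one extra degree of freedom per model and no new data collection. One limit remains: for patients already on an SU at cohort entry, the baseline value may postdate SU start, as it may for the other covariates. If the sponsor prefers to leave the variable out, the article should give the reason.

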## Abstract

**Background:**

Patients with type 2 diabetes (T2D) are at increased risk for developing cancer. As approximately 8% of the world’s population is living with T2D, even a slight increase in cancer risk could result in an enormous impact on the number of persons developing cancer. In addition, several glucose lowering drug classes for treating patients with T2D have been associated with a difference in risk of cancer overall, and especially for obesity related cancers. In what way and to what degree cancer risk is modified by the use of different sulfonylureas (SU) is unclear. The primary aim of this study will be to evaluate within-class SU differences in obesity related cancer risk. Secondary aims will be to investigate within-class SU differences in risk for all cancers combined and site-specific cancers separately (i.e. breast, colorectal, prostate, bladder and lung cancer) and to account for duration-response relationships between individual SU use and cancer risk.

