#### Secondary analyses

In a secondary analyses changes diabetes medication during follow-up will be accounted for. Time dependent cox proportional hazard analyses will be used to estimate the adjusted hazard ratio of developing all cancer when using gliclazide compared to other SUs (both individual and grouped as non-gliclazide SU). Exposure to confounders (including concurrent metformin and insulin use) will be handled as time varying variables where follow-up is available. The updated mean method will be used for HbA1c, BMI and serum creatinine. These analyses will be repeated to investigate the adjusted hazard ratio of breast, colorectal, prostate, bladder and lung cancer.

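### The stated adjustment set names only metformin and insulin among background glucose-lowering drugs; other recorded classes, including thiazolidinediones, appear in no planned adjustment, exclusion, censoring rule or sensitivity analysis

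*Protocol article*

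**What the plan says.** All references are to the protocol article.

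- **Co-variates.** The list is specific. Its only glucose-lowering drugs stand in the run "serum creatinine (continuous), metformin use (yes, no), insulin use (yes/no").
- **Primary analysis.** "The primary analyses will be corrected for the previously mentioned confounders measured at baseline". The primary model therefore takes that list, at cohort entry.
- **Secondary analyses.** The section opens: "In a secondary analyses changes diabetes medication during follow-up will be accounted for". It continues: "Exposure to confounders (including concurrent metformin and insulin use) will be handled as time varying variables where follow-up is available". The same analyses are then repeated for the five sites, bladder among them.
- **ZODIAC (data source).** The recorded items include "medication use (both diabetes-specific and other medication").
- **Abstract, Background.** "several glucose lowering drug classes for treating patients with T2D have been associated with a difference in risk of cancer overall", and the sentence goes on to single out obesity-related cancers.
- **Background.** "the use of pioglitazone, not rosiglitazone, has been linked to the development of bladder cancer in some studies", qualified at once: "the robustness of the evidence underlying this possible relationship remains unclear and was absent in recent reports". The same section counts sulfonylureas (SUs) as one of six oral classes advised after metformin, and says the Dutch guideline prefers gliclazide.
- **Study endpoints.** Bladder cancer is a secondary, site-specific endpoint. It is not in Table 1, which defines the primary endpoint.

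**The concern.** The study compares gliclazide with other SUs in routine care, so the comparison depends on the adjustment set. The article gives the cancer associations of other glucose-lowering drugs as part of its rationale, and its database records diabetes medication. Even so, the adjustment set it states covers only two such drugs.

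If patients on gliclazide and patients on other SUs differ in their use of thiazolidinediones or another add-on class, and that class alters cancer risk, part of its effect would be read as a difference between SUs. Because one SU is preferred by guideline, co-prescribing could plausibly differ by prescriber or period. The clearest case is the bladder-cancer comparison, and the all-cancer comparison through it.

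**Working it through.** **Step 1: does any section deal with the other classes?**

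| Section | Background glucose-lowering drugs dealt with |
|---|---|
| Co-variates | metformin, insulin |
| Primary analysis | the same list, at baseline |
| Secondary analyses | confounders time-varying, metformin and insulin named; medication changes mentioned without drug or method |
| Exclusion | insulin use; apart from that, cancer before SU use and switching between SUs |
| Follow-up | no censoring at start of another drug class |
| Subgroup analyses | metformin only |
| Sensitivity analysis (six) | lag, timing of confounders, early events, complete medication data, complete clinical data, SU switching; no other drug class |

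No section names another class. By the article's own count, 6 − 1 = 5 further oral second-step classes exist.

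**Step 2: is the choice of metformin and insulin explained by stronger evidence?** The Background section discusses three background drugs. For insulin glargine it reports null and inverse studies, for metformin it reports concerns about bias, and for pioglitazone it reports unclear evidence. Insulin and metformin are adjusted for despite that doubt. The article states no criterion that separates the third drug from the other two.

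**Step 3: how large could the bias be?** The article gives no drug-use figures, no event counts and no hazard ratio for any add-on drug, so there is no figure of its own to reproduce. All inputs below are assumptions. For a binary confounder with hazard ratio h, used for a proportion p1 of person-time on gliclazide and p0 on other SUs, the gliclazide hazard ratio is multiplied by

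B = (1 + p1(h − 1)) / (1 + p0(h − 1)).

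| p1 | p0 | h | Calculation | B |
|---|---|---|---|---|
| any | any | 1.0 | 1 / 1 | 1.00 |
| 5% | 5% | any | equal terms | 1.00 |
| 2% | 10% | 1.2 | 1.004 / 1.020 | 0.984 |
| 2% | 10% | 1.5 | 1.010 / 1.050 | 0.962 |
| 5% | 20% | 1.2 | 1.010 / 1.040 | 0.971 |
| 5% | 20% | 1.5 | 1.025 / 1.100 | 0.932 |

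A more extreme assumption (2% versus 20%, h = 2.0) gives 1.02 / 1.20 = 0.85. The direction is also assumed: with the 5% and 20% exchanged at h = 1.5, B = 1.100 / 1.025 = 1.07.

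The formula is for a yes/no SU contrast. The planned model uses cumulative years on each SU, so these factors show an order of magnitude and do not transfer directly to the planned estimate.

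**The case against.** A reader might infer that pioglitazone is an established cause of bladder cancer which the plan knowingly leaves uncontrolled, and that the primary result is therefore biased. The documents do not support that reading:

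- **The link is disputed.** The article reports it from some studies only, and in the same sentence calls the evidence unclear and absent in recent reports. If there is no effect, there is no bias. This stands.
- **Uncontrolled is too strong for the secondary models.** The Secondary analyses section says medication changes will be accounted for, and its list of confounders is introduced by a word that need not be exhaustive. Other classes may be meant. But the text commits to no drug and no method, and the primary model uses baseline covariates only, so the sentence does not reach it.
- **The primary endpoint is not shown to be affected.** Bladder cancer is outside Table 1. The remark on obesity-related cancers in the abstract names no class, and nothing in the article ties an unlisted class to a Table 1 cancer. This stands; for the primary endpoint the point is precautionary.
- **Differential use is undocumented.** Year of cohort entry, diabetes duration and HbA1c are already covariates and would absorb part of any difference by period or disease stage. That reduces the concern. It does not remove it, because year of entry is fixed and cannot follow drugs started later.
- **Add-on therapy during follow-up may depend on how well the SU worked**, so adjusting for it could bring in bias of its own. True, but the plan already accepts this for metformin and insulin in its secondary models.

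An article may leave the coding of covariates to a fuller document. Here, however, it states the adjustment set, and that stated set is what is narrow.

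**Conclusion.** The concern holds in a limited form. The stated adjustment set names metformin and insulin only, and no section commits the study to dealing with any other background glucose-lowering class, although the medication category is recorded and the article itself treats other classes as possibly related to cancer.

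Confounding follows only if use of these drugs differs between SUs after the planned adjustment and if they affect cancer risk. The documents settle neither condition. The size is therefore unknown; illustrative factors run from 1.00 to about 0.93, with larger values only under more extreme assumptions. The bladder analysis has the most specific support, as a secondary endpoint. That pioglitazone in particular is available in the data is inferred from the general medication entry, which does not name it.

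The Discussion argues that even a minimal change in cancer risk matters, so distortions of a few percent are worth guarding against when this can be done cheaply.

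**What to change.** Add two yes/no terms to the Co-variates list: thiazolidinedione use (pioglitazone use in the bladder-cancer model), and use of any other non-SU glucose-lowering drug. Handle both exactly as metformin and insulin are handled: at baseline in the primary model and time-varying in the secondary models. State in the Secondary analyses section that the sentence on medication changes covers these classes.

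A separate rosiglitazone term and censoring at first pioglitazone use are not needed for this. No additional lag is called for either: the plan's one-year lag is described for SU exposure, and nothing in the article lags metformin or insulin.

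Cost: no new data category, and one or two extra terms per model. That is a real cost in the site-specific models, which may be sparse and are run separately for men and women. Where events are too few, use one combined term or report the extra adjustment as a sensitivity analysis. The baseline terms in the primary model will not capture drugs started later; the time-varying secondary models cover those.

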An association between the class of SUs and increased overall cancer risk has also been reported [21–24]. Most previous studies are limited by methodological issues, for example many studies reported baseline SU use and did not account for duration of SU use [22–24]. There is also evidence suggesting within-class SU differences in cancer risk, where gliclazide use has been associated with a lower cancer risk [21–24]. There are several potential mechanistic explanations, one of which could be that gliclazide leads to a more selective glucose dependent insulin response and lower insulin levels. In what way and to what degree cancer risk is modified by different SUs in unclear and requires further investigation and confirmation.

Most evidence, however, is derived from small observational cohort studies and substantial knowledge gaps exist. This also holds true for the presumed favourable long-term cancer safety profile of gliclazide in particular. The relations between use of glucose lowering agents and cancer are complex and there is overlap in risk factors; for example, several glucose lowering agents have been associated with weight gain, which in itself has also been related to an increased cancer risk.

The primary aim of this study is to evaluate within-class SU differences in risk for obesity-related cancer (excluding non-melanoma skin cancers) accounting for weight changes during follow-up and drug exposure [6]. Secondary aims are to evaluate within-class SU differences concerning all cancers combined and the cancer risks of the five largest groups of site specific cancers (breast, colorectal, prostate, bladder and lung cancer) accounting for duration of drug use.

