#### Exposure

Patients will be considered unexposed to SUs until the time of the first SU prescription within ZODIAC. A one-year lag period will be accounted for. A lag period is necessary to take into account a latency time window and to minimise possible detection bias around the time of treatment initiation. Exposure to a SU will be classified according to one of the following, mutually exclusive, categories: gliclazide use, glimepiride use, tolbutamide use, glibenclamide use, non-SU use.

We aim to determine whether there are duration-response relationships between the use of SUs and obesity-related cancer incidence. Duration-response will be assessed in terms of cumulative duration of use, defined as the total number of years of use calculated by summing the durations of yearly prescriptions received between cohort entry and the time of the event and will be used as a time-dependent covariate.

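### Metformin and insulin are adjusted only as yes/no while SU exposure is counted in years, so an effect of co-drug duration can remain in the gliclazide contrast and in the SU duration slopes

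*Protocol article*

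**What the plan says.** Under Primary analysis, "Exposure to SUs will be included as the cumulative number of years exposed to a specific SUs". Under Exposure, duration is the "total number of years of use calculated by summing the durations of yearly prescriptions received between cohort entry and the time of the event", used as a time-dependent covariate with a one-year lag.

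Co-variates lists the two co-drugs as "metformin use (yes, no), insulin use (yes/no)". Under Primary analysis, "The primary analyses will be corrected for the previously mentioned confounders measured at baseline". Under Secondary analyses, "Exposure to confounders (including concurrent metformin and insulin use) will be handled as time varying variables where follow-up is available". The only device that carries covariate history is limited to three measurements: "The updated mean method will be used for HbA1c, BMI and serum creatinine".

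The metformin subgroup is also a split into users and non-users. None of the six sensitivity analyses adds a duration term for either drug. Patients on insulin in addition to an SU at study entry are excluded.

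The Background criticises earlier work because "many studies reported baseline SU use and did not account for duration of SU use". It also says "Metformin has more consistently been associated with a decreased cancer risk", followed by a warning about bias, and it places SUs as a second step after metformin alone.

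**The concern.** Two patients who both take metformin at entry get the same covariate value whether they go on to take it for one year or ten. Their SU years meanwhile grow with follow-up. An indicator shifts the hazard by a constant, so it cannot follow an effect that builds up with time. The SU term, which does build up with time, can absorb what is left over. Because SUs are commonly added to metformin, the two durations tend to rise together.

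The baseline insulin term does even less. With insulin on top of an SU at entry excluded, it has little variation, and insulin started later is not adjusted for in the primary model.

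Two results are exposed: the gliclazide-versus-other contrast, if co-drug use differs between SUs, and the duration-response slope of each SU, a named secondary outcome, even if it does not. This coding is stated in the article, so it is not a detail left to a fuller document.

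**Working it through.** The article gives no event count, effect size or co-medication figures, so there is no planned figure to reproduce. Every input below is an assumption chosen to show the mechanism and its plausible range.

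**Between-SU contrast.** Expected-count Poisson model with a separate baseline term for each of 13 years, base rate 0.012 per year and 7% censoring per year. The truth is log rate = a(t) + M·ln r, where M is total metformin years, r is the metformin hazard ratio per year, and SU has no effect. The fitted model is log rate = a(t) + g·(gliclazide × years on SU) + adjustment terms. The false ten-year ratio is exp(10g). Pre-entry metformin years are spread around the means shown and, by assumption, track diabetes duration.

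| Metformin use, gliclazide / other | Mean pre-entry years | r | Yes/no only | Yes/no + diabetes duration |
|---|---|---|---|---|
| 80% / 50% | 2 vs 2 | 0.95 | 0.934 | 0.934 |
| 80% / 50% | 2 vs 2 | 0.98 | 0.975 | 0.975 |
| 80% / 50% | 4 vs 2 | 0.95 | 0.864 | 0.919 |
| 80% / 80% | 4 vs 2 | 0.95 | 0.904 | 1.004 |
| 80% / 80% | 2 vs 2 | 0.95 or 0.98 | 1.000 | 1.000 |

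The last column is the relevant one, because diabetes duration at entry is a planned covariate. Its rows with unequal use run from about 0.92 to 0.97.

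As a rough check on scale, a 30-point gap in use builds a mean gap of 0.30 × 10 = 3 metformin years over ten years. Then 0.95³ = 0.857 and 0.98³ = 0.941. The yes/no term removes part of this but not all.

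**Effect of counting metformin years.** With in-cohort metformin years, a use-at-entry term and diabetes duration in the model, the 80%/50% ratio returns to 1.00.

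Where the only gap is in pre-entry years (80%/80%, 4 vs 2), in-cohort years plus a use indicator without diabetes duration leave the ratio at 0.905, essentially the 0.904 in the table. In that case diabetes duration does the work. In a further version of the calculation it moved the ratio from 0.91 to 0.97–0.98, and counting in-cohort years added nothing.

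**SU duration slopes.** A separate ten-year expected-count model, with equal co-drug duration across SUs, no true SU effect and no diabetes-duration term, gave these false hazard ratios per SU year:

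| Assumed co-drug effect per year | Baseline yes/no | Time-varying yes/no | Cumulative years |
|---|---|---|---|
| Metformin, log-HR −0.05 | 0.993 (0.93 over ten years) | 0.998 (0.98) | 1.000 |
| Insulin, log-HR +0.05 | 1.005 (1.06) | 1.002 (1.02) | 1.000 |
| None | 1.000 | 1.000 | 1.000 |

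Ten-year values come from unrounded slopes. The gliclazide/other ratio was 1.000 in all these rows. Unequal use is needed to bias the contrast but not to bias the slope.

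**The case against.** The strongest reply is that nothing here is a contradiction. Yes/no adjustment for co-medication is a common modelling choice. Bias in the contrast needs both an effect that grows with years and different use between SUs, and the article documents neither. All patients are SU users, which may narrow the difference in use. Time-varying metformin and insulin and a metformin subgroup are already planned. Most of this stands, and it limits the size of the point. It does not remove the point, because current status carries no count of years and no planned analysis would show whether the count matters.

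Four stronger readings are tempting and are not supported:

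- **Gliclazide is favoured.** The article says only that Dutch guidance prefers gliclazide. It gives no metformin use or duration by SU, so the direction is unknown.
- **The bias is 0.86 or larger at ten years.** That figure leaves out diabetes duration, which is in the plan. Adding it moves the same scenario from 0.864 to 0.919.
- **Former metformin users count as non-users in the primary analysis.** Confounders there are fixed at baseline, so a baseline user stays a user after stopping. The reading could fit only the concurrent-use coding of the secondary models.
- **The plan treats both drugs as established cancer modifiers.** The Background warns of bias for metformin. For insulin it mentions only a disputed link between glargine and breast cancer.

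The objection also holds for insulin. Later insulin may follow from earlier SU treatment, so cumulative insulin in the primary model could adjust away part of the SU effect.

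**Conclusion.** The concern holds in limited form. The mismatch of scales is explicit, and no other section repairs it. It can leave residual confounding in the between-SU contrast if a co-drug has a duration-dependent association with cancer and is used differently across SUs. The first condition alone can bias the SU duration slopes.

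The real size cannot be derived from the article. Under the assumed metformin effects and 80% versus 50% use, it is a false ten-year ratio of about 0.92 to 0.97, and no bias if use and duration are equal. That is modest, but it could matter if the true SU differences are also small. Differences confined to pre-entry metformin years are already largely absorbed by diabetes duration, to the extent that the two track each other, and counting in-cohort years does not cure what remains. The case for a change is good for metformin. For insulin it supports only a cautious sensitivity analysis.

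**What to change.** 1. In the time-varying models under Secondary analyses and the duration-response analysis under Exposure, enter metformin as cumulative in-cohort years, using the same annual rule and one-year lag as SU exposure. Add an indicator for metformin use at entry, and keep diabetes duration in the model.
2. Under Sensitivity analysis, pre-specify a repeat of the primary model with cumulative metformin years, and a separate repeat with cumulative insulin years. State that the insulin version is to be read with care, because later insulin may be a consequence of earlier SU treatment.
3. Keep the yes/no version so that the two can be compared.

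The cost is one derived variable per drug from records already collected annually. Intervals will be somewhat wider because co-drug years correlate with SU years. Metformin use before ZODIAC entry will still be only approximated, and the report should say so.
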